#### 2.2.3. Study Design and Setting

The research is designed as a waitlist-controlled trial, with the implementation of a manualized climbing intervention for Lebanese adolescents and adolescent refugees living in the Bekaa region of Lebanon. The plan is for the CG not to receive any study-specific intervention while the IG receives the intervention, but the CG members will be invited to participate in an upcoming cycle of the climbing program. Members of the CG will, therefore, be offered the same intervention as the IG after their waiting period. For the individual participant, the study duration will be up to approximately 12 weeks with 8 weeks of intervention (see Figure 1), followed by the voluntary participation of the CG members in the intervention. The procedure involves administering surveys to both groups (IG and CG) before the intervention begins (t0, pretest) and immediately after the intervention ends (t1, posttest). During the second half of the intervention period, qualitative semi-structured interviews will be conducted with members of the IG focusing on modes of action and outcomes of the intervention. The participant timeline is presented in Figure 1. Trial Registration Data are presented in Table 1 (ISRCTN13005983, registered April 2022, registered prospectively).

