### 2.4. Screening and Enrollment

To provide access to the climbing program to as many adolescents as possible and to ensure high representativeness of the sample, the adolescents are being recruited through several outreach channels (e.g., schools, other non-profits, social networks of current participants, social media, outreach campaigns in informal tented settlements). Informational material is being distributed and events are being held in schools and refugee camps to inform adolescents about the climbing program. A social media campaign is also being launched. Parents or (legal) guardians can use an online form to apply to participate in the program and, thereby, provide informed consent. If the inclusion criteria are met, the adolescents are then invited to attend a first trial session to determine whether they want to participate. If they are interested in participating, inclusion and exclusion criteria are verified by the study personnel, and the adolescents and their parents are asked to provide written informed consent. The written informed consent of the parents/legal guardians are gathered through personal communication between a trained staff member of ClimbAID and the respective guardian to make sure that every participant and their legal guardians understand the study conditions.

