### 2.6. Allocation to the IG and CG

Due to culture-specific requirements and for organizational reasons, stringent randomization is not possible. For example, due to school exams, many participants are limited to only one of the three cycles. Some female participants are only allowed to participate if they are accompanied by another member of the family. To navigate this and to increase adherence to the intervention, the timing of the intervention (immediately = IG, 3 months later = CG) can be self-selected by participants, providing they are available at each time point when data are being collected. In addition, we are accommodating special requirements (e.g., women-only groups, groups for those who can only participate if accompanied by a specific person). Out of the actual eligible applicants, about 20% stated that their availability was limited to one of the three cycles. We are allowing such applicants to self-select the timing of their participation, thereby determining their classification as either CG or IG participants.

Remaining participants are being allocated randomly. First, each applicant is being assigned a random number by using Microsoft Excel’s “=RAND()” function. Then, applicants are being allocated to the CG or IG based on the parity of the random number’s thousandth digit, whereby if the thousandth digit is even, the applicant is allocated to the CG, otherwise the participant is allocated to the IG. 

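### Section 2.6 draws the arm on applicants, and nothing readable withholds it until written consent and t0, so knowledge of the arm can bias enrolment and the time × group effect

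*Protocol article*

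**What the plan says.** Section 2.6 sets out two routes into the arms. Applicants whose availability is limited choose their timing: "Out of the actual eligible applicants, about 20% stated that their availability was limited to one of the three cycles". They may "self-select the timing of their participation, thereby determining their classification as either CG or IG participants". For everyone else, "Remaining participants are being allocated randomly", and the mechanism is: "First, each applicant is being assigned a random number by using Microsoft Excel’s “=RAND()” function". The parity of one digit of that number then gives the arm. The unit named at the draw is the applicant, although 'participant' also appears in the same paragraph.

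Section 2.4 shows what an applicant is: "Parents or (legal) guardians can use an online form to apply to participate in the program and, thereby, provide informed consent". A first check of the inclusion criteria and a trial session follow. After that, "If they are interested in participating, inclusion and exclusion criteria are verified by the study personnel", and written consent is sought from adolescents and parents at the same step.

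Section 2.2.3 places the baseline relative to the start of the intervention, not relative to allocation: "The procedure involves administering surveys to both groups (IG and CG) before the intervention begins (t0, pretest").

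Section 2.11.1 names mixed ANOVAs (time × group) for the group comparison. The Discussion acknowledges that all outcomes are self-assessed and unblinded. Figure 1 (participant timeline) and Figure 2 (flow chart) are not available in the text reviewed.

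**The concern.** The point concerns the order of steps. It does not concern the random number generator, or the decision to let some applicants choose their timing.

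If the draw is made on the list of applicants and the result is known, two things can go wrong even among those allocated at random.

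- **Enrolment.** A family told to wait can decline at the written-consent step or fail to attend t0. Such a family was never enrolled, so it is outside the assumed 35% dropout and outside both the per-protocol and the intention-to-treat analysis. The arms can then differ in who entered them.
- **Baseline reporting.** Adolescents who know their arm may rate their well-being differently at t0, through disappointment in the CG or anticipation in the IG. Since t0 is half of the time × group contrast, such a shift can masquerade as an intervention effect or hide one. The baseline comparison in section 2.11.1 cannot tell it from chance imbalance.

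Unblinded reporting at t1 is unavoidable in this trial. At t0 it is avoidable for the randomised majority.

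**Working it through.** **Step 1: order of events as worded.**

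| Step | Source | Position |
|---|---|---|
| Online application with the guardian's first consent | 2.4 | makes the family an applicant |
| Trial session, verification, written consent | 2.4 | after application |
| Random draw | 2.6 | on each applicant; position relative to written consent and t0 not stated |
| t0 | 2.2.3 | before the intervention, given to IG and CG; position relative to the draw not stated |

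The draw is worded on a unit that exists before written consent, and t0 is described by arm. Self-selection in 2.6 is conditional on being available at each data collection, which looks forward to t0. The natural reading is that the arm can be known before written consent and t0. No readable sentence rules this out.

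**Step 2: the plan's sample size.** Section 2.7 gives 52 per group at posttest and 80 enrolled. The dropout step reproduces: 52 / (1 − 0.35) = 80. With d = 0.55 and two-sided alpha 0.05, 52 per group corresponds to 80% power (normal approximation; 79% by t test), whereas 90% would need 70 (71 by t test). That is a separate matter; 52 is used here as the plan's analysed number.

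**Step 3: effect of a t0-only shift.** Let b be the between-arm shift at t0 in outcome SDs, absent at t1, and r the pre-post correlation. Neither is in the document; both are assumed. With two time points the time × group test is the t test on change scores:

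- bias in the contrast = b in absolute size
- SD of change = √(2(1 − r)); at r = 0.5 this is 1
- SE = SD of change × √(2/52) = 1 × 0.196 = 0.196
- rejection rate with no true effect = 1 − Φ(1.96 − b/SE) + Φ(−1.96 − b/SE)

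For b = 0.2: b/SE = 1.02, giving 1 − Φ(0.94) + Φ(−2.98) ≈ 0.175. The noncentral t gives 0.173.

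| Assumed b (SD) | False positives, r = 0.5 (normal / noncentral t) | False positives, r = 0.3 to 0.7 (normal) | Power at d = 0.55 if the shift opposes the effect, r = 0.5 (noncentral t) |
|---|---|---|---|
| 0 | 5.0% / 5.0% | 5% | 79% |
| 0.1 | 8.0% / 8.0% | 7.2% to 10.1% | 62% |
| 0.2 | 17.5% / 17.3% | 13.8% to 26.1% | 42% |
| 0.3 | 33.4% / 32.9% | 25.3% to 50.6% | 24% |

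The power column uses a net difference of 0.55 − b.

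**Step 4: selective refusal.** Suppose 10% to 20% of those drawn to wait decline before t0 and differ by 0.5 SD in expected change from those who stay (both assumed). The CG mean moves by 0.10 × 0.5 = 0.05 SD to 0.20 × 0.5 = 0.10 SD.

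**The case against.** The strongest reply is that the order is inferred, not stated. Section 2.6 mixes 'participants' with 'applicants' and also speaks of eligible applicants. Screening and enrolment are described before allocation, and naming IG and CG at t0 may simply label who is surveyed. Figure 1, where the order would normally appear, is not shown. This stands: a reader might infer that the arms were demonstrably formed and announced before t0, and the document does not establish that. It does not remove the point, because the rule as worded acts on applicants and permits that order.

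Second, a reader might infer that families give no consent until they know their arm. Section 2.4 contradicts this, since guardians consent with the online form. Only the later written consent and attendance at t0 could follow disclosure. Waiting families are also offered the programme later, and all participants are rewarded after the posttest, which may keep refusals low.

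Third, the full carry-over in the working needs a shift that is gone by t1. Any part that persists cancels in the change score. Section 2.11.1 also plans regression analyses. If these adjust for t0, only r × b carries over; at r = 0.5 the false-positive rate is then 6.0%, 9.1% and 14.3% for b = 0.1, 0.2 and 0.3 (normal approximation). This too stands, but the mixed ANOVA named for the group comparison takes the shift in full.

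Finally, no rule about order can conceal the arm from the roughly 20% who choose it, and the Discussion already admits incomplete randomisation and unblinded self-report. That is correct, and it limits the remedy to the randomised participants.

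**Conclusion.** The concern holds in a limited form. As worded, section 2.6 allows the arm to be drawn and known before written consent and t0, and no readable text withholds it. For the roughly 80% randomised, this can bias who proceeds to enrolment and can bias the t0 WEMWBS.

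The size is conditional. False positives of about 8% to 33% rest on an assumed t0-only shift of 0.1 to 0.3 SD, r = 0.5, 52 per arm and no true effect; a shift in the other direction costs power instead. The document supports neither a direction nor a size. It would therefore be wrong to read these figures as the trial's actual error rate, or to say that the primary effect is biased rather than open to bias.

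The change is worth making because it protects the only randomised part of the trial at little cost. Confidence is medium, given the mixed wording and the unseen figures.

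**What to change.** Amend section 2.6 along these lines:

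> Participants not choosing their own timing are randomly allocated only after the inclusion and exclusion criteria have been verified, written consent has been given and the t0 questionnaire has been completed. Until then the arm is not known to the family or to staff who enrol participants or administer t0. Participants who choose their timing are excepted and are identified as such in the data.

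If the draw must be made earlier, its disclosure at least should wait until t0 is complete. Replace 'applicant' in the description of the draw by 'enrolled participant with completed t0', bring the text into line with Figures 1 and 2, and count everyone randomised in the flow chart and the intention-to-treat set.

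Table 1 gives recruitment as complete, although sections 2.4 and 2.6 are in the present tense. If enrolment is over, the order cannot be changed. In that case:

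- state the order actually used;
- report, by arm, how many were lost between the draw and t0;
- add a posttest-only comparison among those randomised as a sensitivity analysis. A t0-only reporting shift does not touch it, though it does not remove selective enrolment or unblinded reporting at t1.

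The cost is wording and scheduling, with no added visits, staff or participants. Families learn their start date somewhat later, and groups and transport are planned after t0. The posttest-only analysis has fewer participants: if the 20% applies equally to both arms, 0.8 × 52 ≈ 42 per arm remain.

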### 2.7. Sample Size Estimation

Power calculation was performed using G*Power software [48] (University of Duesseldorf, Germany) with a two-tailed alpha of 0.05, a beta of 90%, and an estimated effect size of Cohen’s d = 0.55. This resulted in a necessary sample (as treated AT) of at least 52 members per group at posttest. 

As the dropout rate is difficult to foresee in the current political and economic situation, we assumed a drop-out rate of 35% per intervention cycle. Thus, we need to enroll 80 participants in the IG and the CG, respectively. Hence, at least 160 adolescents need to be included in the study, distributed across the six climbing groups (each consisting of 12–14 participants) and the control group. Including the waitlist-control group (which will be offered the intervention after the study period), up to a total of 160 adolescents should thus be provided with a climbing program. Figure 2 gives an estimated overview about sample sizes.

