### 2.2. Trial Outcomes and Hypothesis

#### 2.2.1. Primary Outcome

Psychological well-being is being measured with the WEMWBS [44]. The participants in the intervention group (IG) are expected to benefit significantly more in terms of their psychological well-being than adolescents assigned to the control group (CG; effect size of Cohen’s d ≥ 0.55).

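### The stated inputs do not give 90% power: 52 per group at d = 0.55 gives about 79%, so the risk of missing the effect is about double what is implied

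*Protocol article*

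**What the plan says.** Section 2.7 of the protocol article sets the sample size. It says "Power calculation was performed using G*Power software", and gives the inputs as "with a two-tailed alpha of 0.05, a beta of 90%, and an estimated effect size of Cohen’s d = 0.55". The result is "at least 52 members per group at posttest", described as an as-treated number. The next step is dropout: "we assumed a drop-out rate of 35% per intervention cycle", from which "we need to enroll 80 participants in the IG and the CG, respectively", 160 in total.

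The same effect size defines the primary hypothesis in Section 2.2.1, where the intervention group is expected to gain more well-being than the control group with an "effect size of Cohen’s d ≥ 0.55".

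Section 2.11.1 plans mixed ANOVAs (time × group) for the group comparison and makes the per-protocol analysis primary. Neither section gives a correlation between baseline and posttest scores, a covariate adjustment, or the G*Power test family.

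**The concern.** An alpha, a sidedness, a power and a standardised effect fix the size of a two-group comparison of means. The size printed here is well below what those inputs require, so either the power or the number is wrong. The term is also wrong: beta is the probability of a type II error, so a beta of 90% read literally means 10% power. The only sensible reading is 90% power, and the check below uses it.

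The power statement tells readers how to weigh a null result. If they believe the trial had a 10% chance of missing d = 0.55 when the chance was about 21%, they may take a non-significant primary result as stronger evidence against benefit than it is. Section 3 (Discussion) adds to this risk by listing the large sample as a strength, while also noting that a heterogeneous sample may dilute the effect.

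**Working it through.** **Inputs**

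- Two-tailed alpha 0.05, d = 0.55 (SD = 1 on the standardised scale), power read as 0.90: Section 2.7.
- Two independent groups of equal size, 80 and 80 enrolled and 52 and 52 analysed: Section 2.7.
- Dropout 35%: Section 2.7.

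**Step 1. Size needed for 90% power.** The normal approximation is n per group = 2(z₁₋α/₂ + z₁₋β)² / d².

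- 90%, two-sided: 2 × (1.960 + 1.282)² / 0.55² = 69.5, so 70.
- 90%, one-sided: 2 × (1.645 + 1.282)² / 0.55² = 56.6, so 57.
- 80%, two-sided: 2 × (1.960 + 0.842)² / 0.55² = 51.9, so **52**.

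The exact noncentral t calculation gives 71, 58 and 53. The plan's 52 is reproduced only at 80% power with the normal approximation, and is one short of the exact 80% figure. A one-sided test at 90% does not produce it either.

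**Step 2. Power at 52 per group.** The noncentrality is d√(n/2) = 0.55 × √26 = 2.804, with 102 degrees of freedom and a two-sided critical value of 1.983.

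| n per group | Power, d = 0.55, two-sided 0.05 |
|---|---|
| 52 | 0.793 |
| 53 | 0.801 |
| 70 | 0.898 |
| 71 | 0.902 |
| 80 | 0.933 |

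The type II error at 52 is 1 − 0.793 = 0.207. A one-sided test at 52 per group would have power 0.873, still short of 90%.

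**Step 3. Effect detectable with 90% power at 52 per group.** Solving the same noncentral t for d gives 0.642.

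**Step 4. Dropout.** The plan's own step is correct: 52 / (1 − 0.35) = 80. Applied to 71 it gives 71 / 0.65 = 109.2, so 110 per group and 220 in total, against 80 and 160.

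**Step 5. Could a repeated-measures analysis justify 52?** This depends on the baseline–posttest correlation r, which the article does not give, so r is an assumption here. With two time points, the time × group interaction is a comparison of change scores. With d on the posttest SD and equal variances, the standardised effect becomes 0.55 / √(2(1 − r)). For a baseline-adjusted ANCOVA it becomes 0.55 / √(1 − r²). Power at 52 per group:

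| Assumed r | Time × group (change score) | ANCOVA |
|---|---|---|
| 0.3 | 0.65 | 0.83 |
| 0.4 | 0.72 | 0.86 |
| 0.5 | 0.79 | 0.89 |
| 0.6 | 0.87 | 0.93 |
| 0.7 | 0.95 | 0.97 |

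Power reaches 90% at r of about 0.63 for the planned interaction and about 0.52 for ANCOVA. At r = 0.5 the change-score SD equals the posttest SD, so the planned test has exactly the power of the simple t test. Below 0.5 it has less.

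**The case against.** The strongest reply is that 79% belongs to an unadjusted posttest t test, which is not the planned primary analysis. The test family is not named, and Section 2.11.1 names t tests only for secondary outcomes. A model with an unreported correlation could lie behind 52. For example, the between-groups effect of a repeated-measures ANOVA (f = 0.275, half of d) needs 100 participants in total for 90% power at r = 0.4 and 108 at r = 0.5, which brackets the planned 104. G*Power's exact calculation for 80% would have returned 53, so the 80% explanation is not a perfect match either.

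Part of this stands. How 52 arose cannot be settled from the article, and the 79% should be labelled as a two-sample t test figure. The stated inputs still do not lead to 52 at 90%. The between-groups effect averages the two time points and is not the time × group effect that the plan tests. Any rescue needs a correlation that the article does not state, and for the planned test it must be about 0.63 or more.

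A second reply is that posttests from dropouts, imputation and the intention-to-treat sensitivity analysis could bring the analysed number towards 80 per group, where power is 93%. That does not repair the statement: the 90% is attached to 52 as-treated participants, and the primary analysis is per protocol.

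A third reply is that recruitment is listed as complete in Table 1, and that no estimate, test or type I error changes. This is true, and it is why the remedy is a correction to the text.

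**Conclusion.** The point holds. On the inputs printed in Section 2.7, 52 per group gives about 79% power for d = 0.55, not 90%. The type II risk is about 21% against an implied 10%, and 90% power applies to d = 0.64 rather than 0.55. Reaching 90% at d = 0.55 would need 71 analysed per group, or 110 enrolled per group at the plan's dropout rate. Naming 90% as beta is a separate error of terms.

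These figures assume a two-sided comparison of two independent means with equal groups. For the planned time × group test the power at 52 per group depends on the unstated correlation: about 65% at r = 0.3, 79% at r = 0.5 and 95% at r = 0.7.

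**What to change.** Correct the sentence in Section 2.7 and carry the correction into the results paper. No added enrolment is asked for. Suggested wording:

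> With 52 participants per group analysed at posttest, a two-sample t test at two-tailed alpha 0.05 has about 79% power for d = 0.55 and 90% power for d = 0.64.

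Replace *beta* with *power* throughout.

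If the authors wish to keep 90%, they should name the test and state the correlation it requires: at least about 0.63 between baseline and posttest WEMWBS for the planned time × group interaction, or at least about 0.52 if the primary test becomes a baseline-adjusted ANCOVA. If 52 came from a particular G*Power model, its test family and inputs should be reported.

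The cost is one sentence in each paper and a less favourable power figure.

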### 2.11. Data Analysis

#### 2.11.1. Quantitative Data

The data analyses will be performed with the “IBM SPSS Statistics 28” software. To assess the quality of the group allocation, the baseline data from the intervention and control groups will be examined for statistically significant differences. All data will be investigated for plausibility. Participants who drop out of the study but are still available for the posttest will be interviewed subsequently. A missing data evaluation will be carried out, and missing values will be imputed with EM-Imputation [54]. The primary data analytic strategy will be “per protocol”. As a sensitivity analysis, an additional analysis with “intention to treat” will be performed. The level of statistical significance will be set at *p* ≤ 0.05. Mixed ANOVAs (time × group) will be used to determine differences between the groups. Additionally, regression analyses will be used to test the hypotheses and check for possible confounders. Differences between groups will be determined before analysis, and if there are significant differences in important sociodemographic variables, appropriate statistical methods (e.g., propensity score matching) will be used. Secondary outcomes will be tested in an exploratory fashion with *t* tests for independent samples.

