The strengths of the study are the large sample size, the existence of a control group, the mixed-methods approach, the use of manualized treatment options, the naturalistic setting, and therefore, the pragmatic nature of the evaluation of a real-world program. One limitation is the lack of randomization. In this specific study, randomization may also have been a limitation because it may have resulted in the exclusion of female participants for cultural reasons. Being female in a refugee context is a risk factor for mental distress, especially depression [38]. Syrian refugees in Lebanon often live according to religious or cultural traditions with a strong desire to protect girls from potential harmful encounters outside the family. To include female participants, we decided not to randomize the group to allow family members who also need to comply with the inclusion criteria (e.g., mostly brothers, sisters, cousins) to participate together in the same intervention group. In addition, we offered female-only groups, and ClimbAID staff travel on the buses that collect all the participants from their homes. No participants must use public transportation. We therefore concluded that the disadvantages of randomization (which would prevent a vulnerable group from participating in the intervention) outweighed the positives. If the groups differ at baseline in relevant factors, appropriate statistical methods (e.g., propensity score matching) will be applied.

Another potential limitation is that the bouldering intervention cannot be blinded with respect to facilitators or participants. All outcome measures are self-assessed and, therefore, are also not blinded. Third, in the absence of exclusion criteria regarding possible diagnoses or levels of psychological distress, it is possible that we will obtain a heterogeneous sample, with the associated advantages of a naturalistic design and low-threshold intervention and the disadvantages of potentially diluted intervention effects.

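### The intervention arm is treated in six climbing groups, but the sample size and the named tests assume independent participants; if outcomes correlate within groups, the type I error exceeds 5%

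*Protocol article*

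**What the plan says.** Section 2.7 bases the sample size on a two-group calculation "with a two-tailed alpha of 0.05, a beta of 90%, and an estimated effect size of Cohen’s d = 0.55", which gives "at least 52 members per group at posttest". It then states "we assumed a drop-out rate of 35% per intervention cycle" and concludes "we need to enroll 80 participants in the IG and the CG, respectively". The enrolled participants are "distributed across the six climbing groups (each consisting of 12–14 participants) and the control group".

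Section 2.5 describes group delivery: a jointly led warm-up, shared climbing games, paired tasks and group discussion. It also says that the CG has no climbing before its posttest. Section 2.6 allows women-only groups and groups built around a required companion. The Discussion adds that relatives are allowed "to participate together in the same intervention group".

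For the analysis, section 2.11.1 says that time-by-group mixed ANOVAs "will be used to determine differences between the groups". It adds regression for hypotheses and confounders, and independent-samples t tests for the secondary outcomes. The article mentions no ICC, design effect, random effect for climbing group or cluster-robust standard error.

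**The concern.** The programme works through trust, cooperation and communication among the people in a group. One group may gel and another may not. If so, members of the same group share part of their response, and six groups carry less information than the same number of unrelated individuals. CG members have no shared treatment at posttest, so this source of correlation exists in one arm only.

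A mixed ANOVA or t test that ignores this counts group-to-group variation as if it were individual information. The standard error of the IG-CG difference is then too small, the p-value too small and the confidence interval too narrow. This affects the single primary comparison, which is judged at the 5% level. Neither the propensity score matching nor the intention-to-treat sensitivity analysis in section 2.11.1 corrects it, because neither changes how within-group correlation enters the standard error.

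**Working it through.** **Inputs from the article.** Two-sided alpha 0.05, d = 0.55, 52 per arm at posttest, 35% dropout, 80 enrolled per arm, six IG groups of 12–14 (6 × 12 = 72 to 6 × 14 = 84, which fits 80). **Assumed:** the ICC, because none is given; 0.01, 0.05 and 0.10 are shown.

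**Step 1: the plan's own figure.** n per arm = 2(z₁₋α/₂ + z₁₋β)²/d².
- 80% power: 2(1.960 + 0.842)²/0.3025 ≈ 51.9, so 52.
- 90% power: 2(1.960 + 1.282)²/0.3025 ≈ 69.5, so 70 (71 by the exact t test).

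So 52 is the independent-observations figure for 80% power, not for the 90% that section 2.7 appears to intend. That is a separate error and adds no weight here. The dropout step reproduces: 52/0.65 = 80. It leaves no room for a design effect.

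**Step 2: which ICC matters.** With two time points, the time-by-group test equals a t test on change scores. The relevant ICC is therefore that of the change in WEMWBS within climbing groups, not that of its level.

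**Step 3: size of the planned test.** The IG design effect is DE = 1 + (m − 1) × ICC, with m = Σmᵢ²/Σmᵢ. The CG is unclustered and the arms are equal, so true SE / planned SE = √((DE + 1)/2). True size = 2[1 − Φ(1.96/ratio)].
- 52 per arm, groups of 9, 9, 9, 9, 8, 8: m = 452/52 = 8.69.
- 80 per arm, groups of 14, 14, 13, 13, 13, 13: m = 1068/80 = 13.35.

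| Analysed per arm | ICC | DE in IG | SE ratio | True size | Simulated (40,000 runs) |
|---|---|---|---|---|---|
| 52 | 0.01 | 1.077 | 1.019 | 5.4% | 5.4% |
| 52 | 0.05 | 1.385 | 1.092 | 7.3% | 7.2% |
| 52 | 0.10 | 1.769 | 1.177 | 9.6% | 9.5% |
| 80 | 0.01 | 1.123 | 1.030 | 5.7% | 5.8% |
| 80 | 0.05 | 1.618 | 1.144 | 8.7% | 8.5% |
| 80 | 0.10 | 2.235 | 1.272 | 12.3% | 12.3% |

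Retaining more people in the same six groups makes the inflation worse, because the groups are larger.

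**Step 4: power with 52 per arm at d = 0.55.** Two calculations separate two effects.
- Correct SE only, normal approximation, Φ(0.55/√((DE + 1)/52) − 1.96): 80.1%, 78.6%, 72.9% and 66.4% at ICC 0, 0.01, 0.05 and 0.10.
- A valid test that compares the six IG group means with the CG, with Satterthwaite degrees of freedom (simulated): about 75% at ICC 0, and 71%, 66% and 59% at ICC 0.02, 0.05 and 0.10.

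The first row shows the loss from clustering alone. The gap between the rows, about 5 points at ICC 0, is the price of having only six groups to estimate the variance from.

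**The case against.** **No ICC is documented, so inflation is not established.** This stands as a limit on the claim. A reader might infer that the type I error is known to exceed 5%. The article does not support that: the excess depends on a positive ICC of change, and at 0.01 to 0.02 it is one and a half percentage points at most.

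**Stable differences between groups cancel in change scores.** This stands too. A women-only group or a group of relatives may differ in its level of well-being at both time points without biasing the standard error of change. What remains is shared response to treatment.

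**Shared facilitators.** It is tempting to cite them as a further cause. Section 2.5 says that four facilitators lead the activities but does not assign them to particular groups. Facilitators who rotate over all groups would not create variation between groups, so the point does not rest on them.

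**The power loss.** A reader might attribute the whole fall to 71%, 66% and 59% to clustering. Part of it comes from the few degrees of freedom of the valid test, as the value at ICC 0 shows.

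**Model terms may be left to an analysis plan that is not shown, and secondary outcomes are exploratory.** This holds only in part. The article does not just omit a detail: it names the primary test and completes a sample-size calculation, and both assume independence. For the secondary outcomes, strict error control does matter less.

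**The trial has larger weaknesses**, such as self-selected timing for about 20% of applicants. That is true, but it does not make the standard error correct.

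**Conclusion.** The structural point holds on the text alone: collective treatment in six groups in one arm, no treatment in the other before posttest, and a sample size and named tests that assume independence. The consequence is conditional. If the change-score ICC within climbing groups is positive, the planned tests reject too often. The rate is about 5.4% to 9.6% with 52 analysed per arm and about 6% to 12% with 80, for assumed ICCs from 0.01 to 0.10. Below about 0.02 the effect is minor; from about 0.05 it matters for the primary conclusion.

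These figures assume roughly equal group sizes and clustering in the IG only. Relatives may be enrolled in either arm, so some correlation could also exist in the CG; the figures do not include it.

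**What to change.** - **Primary analysis.** Make the WEMWBS comparison a partially nested linear mixed model: a random climbing-group effect in the IG only, each CG member a cluster of one, and Satterthwaite or similar small-sample degrees of freedom. The SPSS mixed-model procedure can fit this. Use the same model for the secondary outcomes.
- **Data.** Confirm that climbing-group membership is in the analysis dataset. The balancing of interviews by intervention subgroup (section 2.1) and the session protocols (section 2.10) suggest that it is known, but section 2.9.2 does not list it among the recorded variables. No family identifier is listed either. Add a family term, in both arms, only if relatives can be identified.
- **Power.** Restate it for a stated ICC range, using the values from the cluster-mean test above. Table 1 lists recruitment as complete, so this will inform interpretation rather than the design.

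**Cost.** A change to the analysis text, one further model term and a check of the data. Intervals will be somewhat wider. With six groups the variance component is poorly estimated and may come out at zero, so the plan should say in advance how that case is handled.
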